## Abstract

**Background:**

Plantar fasciitis is the most commonly reported cause of chronic pain beneath the heel. Management of this condition commonly involves the use of corticosteroid injection in cases where less invasive treatments have failed. However, despite widespread use, only two randomised trials have tested the effect of this treatment in comparison to placebo. These trials currently offer the best available evidence by which to guide clinical practice, though both were limited by methodological issues such as insufficient statistical power. Therefore, the aim of this randomised trial is to compare the effect of ultrasound-guided corticosteroid injection versus placebo for treatment of plantar fasciitis.

**Methods:**

The trial will be conducted at the La Trobe University Podiatry Clinic and will recruit 80 community-dwelling participants. Diagnostic ultrasound will be used to diagnose plantar fasciitis and participants will be required to meet a range of selection criteria. Participants will be randomly allocated to one of two treatment arms: (i) ultrasound-guided injection of the plantar fascia with 1 mL of 4 mg/mL dexamethasone sodium phosphate (experimental group), or (ii) ultrasound-guided injection of the plantar fascia with 1 mL normal saline (control group). Blinding will be applied to participants and the investigator performing procedures, measuring outcomes and analysing data. Primary outcomes will be pain measured by the Foot Health Status Questionnaire and plantar fascia thickness measured by ultrasound at 4, 8 and 12 weeks. All data analyses will be conducted on an intention-to-treat basis.

**Conclusion:**

This will be a randomised trial investigating the effect of dexamethasone injection on pre-specified treatment outcomes in people with plantar fasciitis. Within the parameters of this protocol, the trial findings will be used to make evidence-based recommendations regarding the use of corticosteroid injection for treatment of this condition.

**Trial Registration:**

Australian New Zealand Clinical Trials Registry. ACTRN12610000239066.

## Background

Plantar fasciitis is the most commonly reported cause of chronic pain beneath the heel [1,2]. The condition is characterised by pain at the calcaneal origin of the plantar fascia, made worse by weight-bearing after prolonged periods of rest [1]. The epidemiology of plantar fasciitis in the general population is currently uncertain. An Australian population-based study involving 3,206 randomly selected participants has reported a heel pain prevalence of 3.6% [3]. A North American study of adults aged over 65 years found that 7% had tenderness beneath the heel [4]. It has also been estimated that 1 million physician visits per year in the United States are for the diagnosis and treatment of plantar fasciitis [5]. In addition, the disorder is estimated to account for approximately 8% of all running-related injuries [6,7].

The underlying pathology of plantar fasciitis is poorly understood, though the majority of histological studies report a predominance of degenerative changes at the plantar fascia enthesis. The most common pathological features are deterioration of collagen fibres, increased secretion of ground substance proteins, focal areas of fibroblast proliferation and increased vascularity [8-11]. The presence of biochemical markers of inflammation (e.g. cytokines and prostaglandins) have not been well investigated, however, several studies report non-specific evidence of local inflammatory change [11-13]. As described in relation to tendinopathy [14], it is feasible that plantar fasciitis is a disorder that proceeds through a spectrum of underlying processes. However, evidence for histological change over time is currently lacking, as current studies have only examined specimens obtained from patients undergoing surgery for long-standing symptoms. Therefore, the underlying pathology occurring early in the development of plantar fasciitis is currently unknown.

Plantar fasciitis is commonly described in the literature as a self-limiting condition [1,2]. This view is supported by the findings of a systematic review, in which plantar heel pain was found to resolve over time regardless of treatment type (including placebo) [15]. Nonetheless, plantar fasciitis can be a very painful and disabling condition prior to resolution of symptoms, causing a negative impact on health-related quality of life [16].

Many interventions are used for the management of plantar fasciitis [17] and corticosteroid injection is a common choice among clinicians. Surveys of American podiatrists [18] and orthopaedic surgeons [19] have reported that approximately 75% of respondents used and/or recommended this intervention. In addition, a systematic review found that corticosteroid injection is the second most frequently described treatment for plantar fasciitis in the medical literature [20].

Despite the widespread use of corticosteroid injection for plantar fasciitis, only two randomised controlled trials have tested the effect of this treatment in comparison to placebo injection [21,22]. By using placebo solution as a comparator, these trials were able to control for potential treatment benefits not due to the pharmacological action of corticosteroids. One trial compared the effect of 25 mg prednisolone mixed with lignocaine versus lignocaine alone (placebo), and found a significant difference in pain reduction favouring corticosteroid one month after treatment [22]. No significant differences between groups were detected in this trial at either three or six months after treatment. However, a large proportion of participants were lost to follow-up, so the authors were unable to make conclusions regarding corticosteroid efficacy in the longer term. An earlier trial compared the effect of 25 mg hydrocortisone versus normal saline (placebo), and found no significant difference in pain reduction between groups two months after treatment [21]. However, this trial had a very small sample size (19 participants) and was therefore statistically underpowered to detect clinically worthwhile differences.

The use of ultrasound in clinical practice has become increasingly popular due to decreased equipment costs, and the ability to perform invasive procedures with better targeting of anatomical structures [23]. Other advantages include the production of high resolution images without exposure to ionizing radiation, and the ability to assess tissues with real-time dynamics [23]. Furthermore, in the treatment of plantar fasciitis, corticosteroid injection performed with ultrasound guidance has been shown to produce longer lasting pain relief than injection guided by palpation [24].

The findings of existing clinical trials provide some support for the use of corticosteroid injection in the short-term management of plantar fasciitis [1,15]. However, a recent systematic review concluded that the effectiveness of this treatment has not been sufficiently established [17], indicating that further research is required. Therefore, the aim of this trial is to investigate the effectiveness of ultrasound-guided corticosteroid injection for treatment of plantar fasciitis over a 12 week period.

## Methods

The trial has been registered on the Australian New Zealand Clinical Trials Registry (ACTRN12610000239066). Recruitment of participants commenced on 3^rd ^June 2010 and is expected to continue until March 2011.

### Ethical approval

The La Trobe University Human Ethics Committee has approved the trial (Application Number: 09-062) and all participants will provide written informed consent prior to enrolment. Ethical standards will adhere to the National Health and Medical Research Council (NHMRC) National Statement [25] and the World Medical Association's Declaration of Helsinki [26]. Publications associated with the trial will be formatted according to the CONSORT Statement [27].

### Setting and eligibility criteria

The trial will be conducted at the La Trobe University Podiatry Clinic and will recruit local community-dwelling participants by multiple newspaper advertisements. Participants will be required to have a clinical history of pain beneath the heel for at least eight weeks prior to enrolment, and to report a minimum heel pain magnitude of 20 mm on a 100 mm visual analogue pain scale. On clinical examination, participants will also be required to report sensitivity to palpation of the medial calcaneal tubercle and/or the proximal plantar fascia. To confirm the diagnosis of plantar fasciitis, the dorso-plantar thickness of the plantar fascia will be measured by ultrasound at a standard location where the fascia crosses the anterior aspect of the inferior calcaneal border. Participants will be required to have a plantar fascia thickness value of 4.0 mm or greater [28]. Finally, participants will be required to attend the second visit (during which a tibial nerve block and heel injection will be given) with a friend or family member who is able to provide transportation from the clinic.

Applicants will be excluded from the study if they have received a corticosteroid injection for plantar fasciitis within the previous six months, or if they have any of the following: a known hypersensitivity to lignocaine hydrochloride or corticosteroids, current skin or soft tissue infection near the injection site, posterior heel pain, current pregnancy, systemic inflammatory disease, diabetes mellitus, previous local surgery, or a history of local trauma. Applicants will also be excluded if they are unable to walk household distances without the use of an aid, or if they have commenced any treatment regimen for plantar fasciitis within four weeks prior to enrolment.

Screening of applicants according to these criteria will occur by a preliminary telephone interview, followed by clinical examination at the initial visit. After a detailed explanation of the study protocol, eligible applicants will be invited to participate in the trial. However, prior to enrolment, all applicants will be assessed for competence to give consent by use of the Evaluation to Sign Consent (ESC) tool [29]. The ESC is specifically designed for use in clinical research and has been shown to have good inter-rater reliability (Pearson *r *= 0.81) [30]. A range of descriptive characteristics will also be collected at the initial visit after enrolment (Table 1). Participants will then be scheduled to attend a second appointment (approximately one week later) where baseline measurements will be taken and the trial intervention performed (Figure 1).

**Table 1 T1:** Descriptive characteristics

Age
Sex
Height
Weight
Body Mass Index (BMI)
Duration of symptoms
Previous and current treatments

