### Data analysis

Statistical analyses will be undertaken using SPSS software (version 14.0 or later, SPSS Corporation, Chicago, IL, USA). Continuous data will be explored for normality using standard tests to satisfy the assumptions of parametric statistics. All analyses will be conducted on an intention-to-treat basis and missing follow-up data will be replaced with baseline observations carried forward (BOCF) (i.e. baseline data will be carried forward in circumstances where follow-up observations are missing). In comparison to a last observation carried forward (LOCF) approach, BOCF has been shown to provide a more conservative estimate when analysing the treatment effect of pain-relief medication [36]. Continuous outcomes with a normal distribution will be analysed using a linear regression technique with baseline measurements adjusted for by the analysis of covariance model (ANCOVA) [37]. If data is found to be not normally distributed, transformation will be attempted. However, if data is still not normally distributed after transformation, non-parametric statistical tests will be used. Other data (nominal or ordinal) will be analysed using appropriate non-parametric statistical tests. Statistical significance for hypothesis tests will be set at the conventional level of 0.05.

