## Discussion

### Mode of action

In the treatment of musculoskeletal disorders, corticosteroid injection is typically used to inhibit synthesis of arachidonic acid from membrane phospholipids, thereby suppressing prostaglandin-mediated inflammation and pain [38]. However, as described previously, histological studies indicate that plantar fasciitis is predominantly a degenerative disorder, with limited involvement of chronic inflammatory processes. Consistent with these findings, absence of inflammation is also reported in the tendinopathy literature [14], and the precise mechanism of pain in tendinopathy remains uncertain [39]. Several alternatives to prostaglandin-mediated pain have been suggested in relation to tendon models, including neurovascular in-growth [40], up-regulation of excitatory neurotransmitters (e.g. substance P, glutamate and acetylcholine) [14,39-41], and increased presence of biochemical irritants (e.g. chondroitin sulfate) [39].The action of corticosteroids on these mechanisms is currently unclear [42], however, corticosteroids have been shown to inhibit fibroblast proliferation and expression of ground substance proteins [14,38]. It is possible that these known effects may be of benefit in the treatment of plantar fasciitis, as increased fibroblast proliferation and excessive secretion of proteoglycans are commonly reported features of the condition. Based on similar reasoning, corticosteroids have been suggested as potentially beneficial for treatment of early-stage tendinopathy [14].

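### Symptom duration is recorded before treatment and is plausibly prognostic, but the stated ANCOVA adjusts only for baseline measurements; adding duration as a covariate would give a small, nearly free gain in precision

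*Protocol article*

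**What the plan says.** **Entry.** The protocol article (Setting and eligibility criteria) asks for a "clinical history of pain beneath the heel for at least eight weeks prior to enrolment" and sets no maximum. Apart from a recent corticosteroid injection, the only bar relating to non-surgical treatment history applies to applicants "if they have commenced any treatment regimen for plantar fasciitis within four weeks prior to enrolment". Nothing requires that earlier treatment was tried or failed.

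**Data collected.** The same section states: "A range of descriptive characteristics will also be collected at the initial visit after enrolment (Table 1"). Table 1 lists duration of symptoms and previous and current treatments. Baseline measurements are taken separately, at the second visit about a week later, when the injection is given.

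**Analysis.** Continuous, normally distributed outcomes are to be analysed by a "linear regression technique with baseline measurements adjusted for by the analysis of covariance model (ANCOVA"). No other covariate is named. The Randomisation section describes a computer-generated sequence and mentions no stratification.

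**Context.** The Abstract remarks: "Management of this condition commonly involves the use of corticosteroid injection in cases where less invasive treatments have failed". The aim at the end of the Background covers plantar fasciitis in general. The Background also reports that heel pain was found to resolve over time under any treatment, placebo included, and that "it is feasible that plantar fasciitis is a disorder that proceeds through a spectrum of underlying processes".

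**The concern.** The entry rule can place a participant with eight weeks of pain beside one with several years of it. If the condition tends to resolve, time since onset may carry information about where pain will stand at 4, 8 and 12 weeks, beyond what the baseline pain score shows. The plan collects this variable before treatment and then gives it no part in the one model it specifies.

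What is at stake is precision. Outcome variation that duration could explain stays in the residual, so the confidence interval is somewhat wider than it need be. In a trial of 80 participants designed for 80% power, a small gain from data already in hand is worth taking. There is also a lesser matter of applicability. The Abstract places injection after less invasive treatment has failed, the entry criteria do not require this, and the Conclusion does not mention the population among the features that may limit generalisation.

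**Working it through.** **Inputs from the protocol article (Sample size):** difference 13 FHSQ pain points, SD 20, alpha 0.05 (taken as two-sided), 80% power, 5% loss to follow-up, 40 per group.

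**Assumed, because the document gives no figure:** correlation of baseline with follow-up pain, r = 0.5; partial correlation of duration with follow-up pain after baseline adjustment, p = 0.2 to 0.3.

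**Step 1. The plan's own figure.** n per group = 2 × (1.960 + 0.842)² × (20/13)² = 37.2, rounded up to 38. Allowing for 5% loss, 38/0.95 = 40. The stated 40 per group reproduces. Power with 38 per group is 79.9% by the t-test.

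**Step 2. Power under the planned ANCOVA.** The sample size section says that the gain from covariate adjustment was left out, so the right starting point is not 80%. Residual SD = 20 × √(1 − 0.5²) = 17.32. Standardised difference = 13/17.32 = 0.75. Power with 38 per group is about 90%.

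**Step 3. Adding duration.** Residual variance is multiplied by 1 − p².

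| Partial correlation p | Variance cut | Residual SD | Power, 38 per group |
|---|---|---|---|
| 0 (planned model) | 0% | 17.32 | 90% |
| 0.2 | 4% | 17.32 × √0.96 = 16.97 | 91% |
| 0.3 | 9% | 17.32 × √0.91 = 16.52 | 92% |

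The standard error falls by 1 − √0.96 = 2% to 1 − √0.91 = 5%. That is worth 1/0.96 − 1 = 4% to 1/0.91 − 1 = 10% more participants. Under a weaker assumed baseline correlation of 0.3, the same steps give 83% for the planned model and 85 to 87% with duration added.

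**Step 4. Why this is not a bias.** With 40 per arm, the chance difference between arms in mean duration has standard deviation √(2/40) = 0.224 SD units. At a correlation of 0.3 (assumed, before any adjustment), a difference of that size moves the pain contrast by 0.3 × 20 × 0.224 = 1.34 points. The unadjusted standard error of the contrast is 20 × 0.224 = 4.47 points, and 1.34²/4.47² = 0.09. This is the same kind of 9% share of variance as in Step 3, and the reported standard error already contains it. Adjustment removes that share; it does not correct an error.

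**Step 5. A subgroup analysis would be weak.** For two equal halves (19 per arm in each), the standard error of a treatment-by-duration interaction is 20 × √(4/19) = 9.18 points. For an interaction as large as the full 13 points, 13/9.18 − 1.96 = −0.54, which is about 29% power before any covariate adjustment.

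**The case against.** Adjusting for the baseline score is a recognised primary analysis and needs no further covariate to be valid. Further covariates are often left to an analysis plan, which may exist and is not shown. The article also gives no data on how duration relates to outcome; it says that evidence of tissue change over time is lacking. If duration adds nothing, adjusting for it gains nothing.

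Much of this stands: it keeps the point small and confines it to precision. It does not remove it. The article names its model and its covariate, and it separates baseline measurements from the descriptive characteristics that include duration. Whether duration is prognostic depends on the natural course of symptoms, which the Background does address.

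Three stronger readings are tempting, and the document supports none of them.

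- **The trial recruits the wrong patients.** A reader might infer a target population from the Abstract's reference to "corticosteroid injection in cases where less invasive treatments have failed". That sentence describes common practice. The stated aim is plantar fasciitis in general, and the entry criteria fit it.
- **The result is biased by early cases or by chance imbalance in duration.** Improvement in both arms does not by itself bias the difference between them, and chance imbalance is covered by the standard error (Step 4).
- **The plan should test whether early cases respond differently, or rest its recommendations on those who failed other care.** The Discussion does say that "corticosteroids have been suggested as potentially beneficial for treatment of early-stage tendinopathy", but this concerns tendinopathy and, if anything, favours admitting early cases. The interaction would have about 29% power, and Table 1 records which treatments were used, not whether they failed.

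**Conclusion.** The point holds as a modest improvement to the analysis, not as a flaw in design or validity. The stated model leaves out a covariate that is recorded before treatment and is plausibly prognostic on the article's own account. Under the assumed correlations, including it would take power from about 90% to about 91 to 92% for the 13-point difference. If duration proves unrelated to outcome once baseline is in the model, the benefit is nil. The sample size of 40 per group is correct and unaffected.

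The distance between the Abstract's description of practice and the entry criteria is a minor matter of applicability. The share of participants with short or untreated symptoms is unknown, so its practical weight cannot be judged from the document.

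**What to change.** In Data analysis, state before unblinding that the ANCOVA for each continuous outcome will include symptom duration beside the baseline value of that outcome. The log scale is sensible because durations with a floor of eight weeks and no ceiling are likely to be skewed. The cost is one model degree of freedom and a sentence of text. With about 76 evaluable participants, the loss if duration is uninformative is negligible: the standard error would grow by roughly √(1 + 1/72) − 1, which is 0.7%. No new data or visits are needed, and neither the sample size nor the entry criteria change.

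Optionally, add to the limits on external validity in the Conclusion that failure of less invasive treatment was not an entry criterion. No failed-treatment covariate, interaction test or subset-based recommendation is called for.

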### Primary outcomes

Primary outcomes will be pain and plantar fascia thickness at 4, 8 and 12 weeks. Pain will be measured by the foot pain domain of the Foot Health Status Questionnaire (FHSQ), which has been shown to have a high degree of internal consistency (Cronbach's α = 0.88) and test-retest reliability (intra-class correlation coefficient = 0.86) [33]. Participants treated for bilateral plantar fasciitis will be asked to describe symptoms without specific reference to an individual foot (i.e. bilateral pain will be evaluated as one independent sample). Plantar fascia thickness will be measured by ultrasound at a standard location where the fascia crosses the anterior aspect of the inferior calcaneal border (Figure 2). This measurement technique has been shown to have good intra-rater reliability, with the 95% limits of agreement ranging from -0.7 mm to 0.5 mm [34]. Participants treated for bilateral plantar fasciitis will have thickness measurements taken for each individual foot. However, for bilateral cases, the mean change in plantar fascia thickness for the two feet will be calculated at each follow-up in order to evaluate data as one independent sample. Plantar fascia measurements and ultrasound guided injections will be performed with a variable frequency (5-10 MHz) linear array transducer (Acuson Aspen, Siemens Medical Solutions, Pennsylvania, USA).

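### The thickness ANCOVA adjusts only for the second-visit reading, although an eligibility scan at the same site is also available before injection; using both would give a small, free gain in precision

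*Protocol article*

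**What the plan says.** Under Setting and eligibility criteria, thickness is scanned to confirm the diagnosis ("To confirm the diagnosis of plantar fasciitis, the dorso-plantar thickness of the plantar fascia will be measured by ultrasound at a standard location"), with a threshold for entry: "Participants will be required to have a plantar fascia thickness value of 4.0 mm or greater". Screening starts with a telephone interview, "followed by clinical examination at the initial visit", so the entry scan belongs to the first visit. Enrolled participants then return for a "second appointment (approximately one week later) where baseline measurements will be taken and the trial intervention performed".

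Under Primary outcomes, thickness is one of two primary outcomes, at 4, 8 and 12 weeks, and the site is the one used at entry: "Plantar fascia thickness will be measured by ultrasound at a standard location where the fascia crosses the anterior aspect of the inferior calcaneal border". The same section reports "good intra-rater reliability, with the 95% limits of agreement ranging from -0.7 mm to 0.5 mm". For bilateral cases it averages the change in thickness over the two feet.

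Under Data analysis, continuous outcomes are analysed by a "linear regression technique with baseline measurements adjusted for by the analysis of covariance model (ANCOVA". The entry scan has no stated role beyond eligibility. The Sample size section rests on FHSQ pain alone. It acknowledges that covariate adjustment adds precision but leaves this out of the calculation.

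The article does not list which measurements are taken at the second visit. That they include thickness is inferred, because both a change in thickness and a baseline-adjusted thickness analysis need a baseline value.

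**The concern.** Reading error in a baseline covariate weakens its correlation with follow-up and leaves noise in the group comparison that a better covariate would remove. Two readings of the same quantity, about a week apart and both before injection, are expected for each participant, but only one enters the model. Thickness has no power calculation of its own, so free precision is worth having there. At stake is the width of the confidence interval for one primary outcome, not the validity of the comparison.

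**Working it through.** **The plan's own figure.** For FHSQ pain, two-sided alpha assumed: n per arm = 2 × (20/13)² × (1.960 + 0.842)² = 37.2, so 38; 38/0.95 = 40 per arm, 80 in total. The stated sample size reproduces and is not affected by this point.

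**Reading error, from Primary outcomes.** Limits of agreement of -0.7 to 0.5 mm give an SD of differences of (0.5 + 0.7)/(2 × 1.96) = 0.306 mm. The error SD of one reading is 0.306/√2 = 0.216 mm, and the error variance is s² = 0.0469 mm².

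**Assumptions, not in the document.** Between-person SD (b) of 0.7, 0.9 or 1.2 mm; true baseline to follow-up correlation (r) of 0.6, 0.75 or 0.9; independent reading errors; the same error at follow-up.

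**Follow-up thickness as outcome.** The reliability of one reading is R1 = b²/(b² + s²), and of the mean of two R2 = b²/(b² + s²/2). Residual variance is proportional to 1 − r²·R1·R1 with the single baseline and to 1 − r²·R1·R2 with the mean of two.

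Middle case (b = 0.9, r = 0.75):
- R1 = 0.81/0.8569 = 0.945 and R2 = 0.81/0.8334 = 0.972.
- Single baseline: 1 − 0.5625 × 0.945² = 0.497.
- Mean of two: 1 − 0.5625 × 0.945 × 0.972 = 0.483.
- Ratio 0.972, a reduction of 2.8%.

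The entry reading is truncated at 4.0 mm, so all nine cases were also simulated with that selection (2 million draws; assumed mean thickness 5.0, 5.5 and 5.8 mm for the three SDs):

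| Case | Reduction in residual variance | 80 participants count as |
|---|---|---|
| b = 1.2, r = 0.6 (least) | 0.8% | 80/0.992 = 80.6 |
| b = 0.9, r = 0.75 (middle) | 2.8% | 80/0.972 = 82.3 |
| b = 0.7, r = 0.9 (most) | 9.0% | 80/0.910 = 87.9 |

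Confidence-interval width scales with the square root of the ratio: 1 − √0.972 = 1.4% narrower in the middle case and 1 − √0.910 = 4.6% at most. A comparison with 80% power would have about 80.3% to 83.6%. A wider assumed range (b from 0.5 to 1.25 mm), with or without 0.2 to 0.3 mm of week-to-week variation, gives about 1% to 12%.

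**Change from the second-visit value as outcome.** With the second-visit value as covariate, ANCOVA on change and on follow-up give the same treatment effect and residual variance. If the mean of two readings replaces it, part of the second-visit error stays in the outcome. Residual variance then rises by (s²/2)(1 − r²·R1·R2). In the middle case this is 0.0234 × 0.483 = 0.0113, against a residual variance of 0.497 × 0.8569 = 0.426, a rise of 2.7%. Over the range the rise is about 1.5% to 4.4%.

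**Both readings as separate covariates.** Simulation with selection gives the same reduction as the mean does for follow-up thickness, and with the second-visit value in the model this holds whichever outcome is used. The cost is one residual degree of freedom: 77/76 = 1.013, or about 1.3% at n = 80.

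**The case against.** The strongest objection is that ANCOVA on a single pre-treatment baseline is standard and valid, and that the gain is small and rests on two quantities the document does not give. This stands, and it sets the weight of the point. The upper end needs a true correlation of 0.9 over follow-up in a condition whose thickness is expected to change.

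A second objection also stands and shapes the fix. The bilateral rule under Primary outcomes suggests that change may be the analysed variable. If so, swapping in the mean of two readings loses precision, so the outcome has to be named together with the covariate.

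Some inputs are less firm than they look. The limits of agreement are intra-rater, and the article does not say who performs the entry scan. It also does not say that both feet are scanned at entry in bilateral cases, so a fallback is needed. Averaging two feet already reduces reading error, so the gain is smaller there. Baseline observations carried forward for 5% of participants change the result little.

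That the entry reading is selected at 4.0 mm is no bar to using it as a covariate: selection precedes the injection and is the same in both arms. It is a reason not to let that reading define change.

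It could be said that the covariate is a matter for an analysis plan. But the article does state the covariate, and the point concerns that stated choice, not missing detail.

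**Conclusion.** The point holds as a minor, nearly costless improvement. Using both pre-injection readings cuts the ANCOVA residual variance for follow-up thickness by about 1% to 9%, with about 3% in the middle case. This rests on the 0.22 mm error implied by the protocol, the assumed SD and correlation ranges, and the inference that thickness is measured again at the second visit.

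A reader might infer that the planned analysis is biased, invalid or underpowered because it ignores the entry scan. The documents do not support that: adjusting for baseline alone is sound, and the sample size for pain reproduces. A reader might also infer that the mean of two readings is better whatever the outcome. That is not so when change from the second-visit value is analysed.

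**What to change.** In Data analysis, add for plantar fascia thickness: the ANCOVA outcome is follow-up thickness, not change, averaged over treated feet in bilateral cases. The single covariate is the mean of the two pre-injection readings (eligibility scan and second-visit baseline), combined over feet in the same way. For any foot not scanned at entry, use the second-visit value. Keep the second-visit value for describing change and for carrying baseline forward.

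If change from the second-visit value is kept as the outcome, enter both readings as separate covariates instead. That costs one degree of freedom, about 1.3% at n = 80, which cancels the gain in the least favourable cases.

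The cost is a sentence or two of text, best fixed before unblinding. No new visit or scan is needed, given that thickness is measured at both visits.
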